#### Secondary endpoints

*Three parameters will be used to evaluate the child’s assessment of EMONO during the first session of care:*
VAS (Visual analogue scale): the patient marks on the line the point he/she feel represents their perception and eventually their appreciation of contact with EMONOChoice of the child with an adapted drug-liking test: the patient will be asked if he/she prefers to exchange the toy that he/she traditionally receives at the end of the care against an EMONO inhalation without care [38, 39]The child’s will to continue care in the case of adverse effects

*Three parameters will define children who experience both analgesia and anxiolysis during the first session of care:*
Decreased score on the anxiety scale (Venham modified by Veerkamp) before and after inhalation of EMONOPresence of anxiolysis among the effects feltPresence of analgesia among the effects felt

We will estimate the prevalence of children for whom at least one of the first two parameters and the third parameter are present during the same session of EMONO use.

*The parameter “Presence of signs that the child is trying to prolong contact with EMONO” will be used to define patients with a higher appetite for EMONO (shown by patients’ attempt to extend the duration of EMONO use physically or verbally) during the first session of care. The following three parameters will characterize these children:*
Table answering the questions about the presence of expected effects of EMONO and their perceptionsMedical historyFamily situation of parents and anxiety of parents [40–42]

*Three parameters will make it possible to evaluate the impact of the difference of practice between the French dental service university hospitals regarding the anxiety during the first and last sessions of care:*
Decreased score on the anxiety scale (Venham modified by Veerkamp) before and after inhalation of EMONOUse of a sedative premedicationPatient management using closed boxes or open spaces

The different practices evaluated in the French dental service university hospital will include the use or absence of a sedative premedication and management of the patient in closed or open boxes.

The evolution of the EMONO intake between the first and last sessions of care will be evaluated by the existence of an amnesic effect during the last session, tolerance during the history of care (noticed during the last session), difference in the effective dosage between the first and last sessions and the regular concern of the child for EMONO consumption according to the parents during the last session. The difference in EMONO appetite between the first and last sessions will also be recorded.

### Study size

The evaluation of the effects sought and felt by children when EMONO is used in paediatric dentistry does not require any sample size calculation. The dental service of Nantes University Hospital manages between 8 and 10 patients eligible for research per week and has a national average of numbers supported by participating dental services.

This estimate allows a 12-month inclusion potential, which represents between 5000 and 6000 patients. Considering a ratio of one eligible patient out of three to four to include, the recruitment aim is 1300 patients. The period of inclusion was set at 12 months to ensure that the study would be proposed to a maximum of eligible patients.

### Statistical methods

All the evaluation parameters will be subjected to a descriptive analysis. The quantitative variable evaluation parameters will be described using position parameters (mean or median) and dispersion (standard deviation, interquartile range and range). Normality of their distribution will be assessed (normality test and evaluation using the relevant graphic tools). The qualitative variable evaluation parameters will be shown in the form of number and frequency tables for each modality.

To answer the main objective (description of the effects felt and sought using EMONO), the prevalence of each effect felt will be calculated, and the proportion of patients who felt this effect and found it pleasant (positive) will also be indicated.

Each criterion to evaluate the EMONO’s assessment by the child will be analysed independently (average for the VAS score, prevalence of drug-liking and continuation of care).

The prevalence of children who experience both analgesia and anxiolysis will be estimated. A multivariate logistic regression model will be applied to define the associated factors: child/parent socio-demographic characteristics and antecedents.

The prevalence of children with a higher appetite for EMONO will be estimated. A multivariate logistic regression model will be applied to define the associated factors: socio-demographic child/parent characteristics, medical history, presence of expected EMONO effects and their perceptions.

The impact of care practices (sedative premedication and closed/open box management) on anxiety will be evaluated using average comparisons (Student’s tests) of the anxiety score before and after the inhalation of EMONO. A comparison will also be made on the difference in the pre- and post-inhalation score.

The evolution of EMONO intake between the first and last sessions will be described in terms of the prevalence (amnesic effect, tolerance, concern), appetite difference and difference between the effective dosage at the first and last treatment sessions will be calculated.

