## Background

EMONO is an equimolar mixture of oxygen and nitrous oxide available in France for dental care. It has an analgesic effect with a reduction of the perception threshold of different painful stimuli and an anxiolytic effect. It causes modifications in consciousness: patients are relaxed, sedated and less aware of their surroundings. Pulmonary absorption and elimination of nitrous oxide occur very quickly because of its low solubility in blood and tissues, explaining the rapidity of the analgesic effect and quick return to the initial status after discontinuation of inhalation [1–5].

Based on the product characteristics summary available in the French government’s public drug database [base-donnees-publique.medicaments.gouv.fr/], EMONO indications in dentistry are dental care for infants, children and adolescents, as well as for anxious and patients with disabilities. Administered in combination with oxygen, it improves the cooperation of patients during anxiety-related or painful medical and paramedical procedures (mild to moderate pain) and offers a short duration per use. EMONO in dental care provides great benefit to patients with behavioural disorders, mental retardation or excessive anxiety. Patient cooperation tends to improve under EMONO and, when not used in conjunction with psychotropic agents [6–8], the use of EMONO is safe.

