#### Primary endpoint

Our primary endpoint, to describe the effects of EMONO that are felt and sought during care during the first and last treatment sessions, will be performed by questioning the patients comprehensively about the presence or absence of each expected effect of EMONO (waking state preserved, no abolition of judgment, relative analgesia, anxiolysis), and each adverse event (slight decrease in consciousness, agitation, anxiety, euphoric effect, nausea or vomiting, sensation distortion) at the first and last treatment sessions. The presence of unexpected “other” effects will also be indicated. When scored as present, all effects will be considered as experienced by the patient.

For each effect felt, the patient will be asked about his or her perception of the effect (positive or not).

To describe the effects felt and sought with EMONO use, the prevalence of each effect felt will be calculated, and the proportion of patients who felt this effect and found it pleasant (positive) will also be indicated.

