MEOPAeDent is the first study that proposes to evaluate the appetite for the use of EMONO in the French paediatric population in need of dental care, in addition to evaluate the effects sought and felt by children. We believe that this substance evaluation known for its very important contribution in paediatric dentistry will confirm its safety of use and justify its framework of application.

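### The primary prevalences pool children with and without a sedative premedication, so they describe routine practice but cannot be read as the effects or safety of EMONO alone

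*Protocol article*

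**What the plan says.** Under Primary endpoint, the protocol article has children answer yes or no for two lists of effects. The first holds every "expected effect of EMONO (waking state preserved, no abolition of judgment, relative analgesia, anxiolysis". The second list is for unwanted effects, and reduced consciousness belongs to it; it holds "each adverse event (slight decrease in consciousness, agitation, anxiety, euphoric effect, nausea or vomiting, sensation distortion". The counting rule is: "When scored as present, all effects will be considered as experienced by the patient". The section has no rule about drugs given alongside EMONO.

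Statistical methods turns this into the main analysis: "To answer the main objective (description of the effects felt and sought using EMONO), the prevalence of each effect felt will be calculated". The share of children who felt the effect and found it pleasant is reported too. Neither figure is split by any covariate.

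Sedative premedication appears under Secondary endpoints, for the objective on differences between hospitals. The practices compared "will include the use or absence of a sedative premedication and management of the patient in closed or open boxes", at the first and last sessions. Statistical methods uses premedication only for that objective, in Student's tests on the anxiety score. It is not named among the factors of the regression for combined analgesia and anxiolysis, which are socio-demographic characteristics and antecedents. The Eligibility criteria do not exclude premedicated children.

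The Background limits its statement that EMONO is safe to use "when not used in conjunction with psychotropic agents". The closing paragraph of the Discussion expects that the evaluation "will confirm its safety of use and justify its framework of application", and the Discussion part of the Abstract states a similar purpose.

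**The concern.** A recorded co-exposure that can plausibly produce some of the primary outcomes plays no part in the primary result. Anxiolysis is listed as an expected effect of EMONO and a slight decrease in consciousness as an adverse event. A sedative may contribute to either. In a premedicated child the questionnaire cannot separate the two sources.

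Two things are at stake:

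- **Interpretation.** Each pooled prevalence depends partly on how many premedicated children the 12 hospitals enrol. Another setting with a different premedication practice could see different figures even if EMONO acted identically.
- **Safety.** The conclusion the article looks forward to concerns EMONO as a product. A single pooled prevalence of decreased consciousness merges the situation the Background calls safe with the one it sets apart.

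The comparison of anxiety scores by premedication does not fill the gap. It concerns a score on an anxiety scale, not the effects the child reports feeling.

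**Working it through.** **Does the pooling follow from the text?** Four statements, read together, give it:

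1. Eligibility criteria: premedicated children may enter.
2. Secondary endpoints: premedication is recorded at the first and last sessions and differs between hospitals.
3. Primary endpoint: every effect scored as present counts, whatever else was given.
4. Statistical methods: one prevalence per effect, with premedication used only for the anxiety score.

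**Inputs.** The article gives no figure for this point. It does not state the share premedicated (s), or the difference in prevalence between children with and without premedication (u). What it does give is:

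- a recruitment aim of 1300 (Study size);
- pilot anxiolysis of 62% (Discussion), not stated to come from children without premedication;
- a requirement of 1291 patients for the appetite objective (Discussion).

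The last figure matches a precision calculation at the pilot's 16%, if a half-width of 2 points is assumed: 1.96² × 0.16 × 0.84 / 0.02² = 1290.8, rounded up to 1291. It concerns appetite and has no bearing on the pooling.

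**Size of a shift.** With p the prevalence without premedication:

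pooled prevalence = (1 − s) × p + s × (p + u) = p + s × u

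The shift in points, s × u, does not depend on p. Illustrations with p set at 62% (s and u are assumptions):

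| s | u (points) | Shift (points) | Pooled |
|---|---|---|---|
| 5% | +10 | +0.5 | 62.5% |
| 10% | +20 | +2 | 64% |
| 20% | +20 | +4 | 66% |
| 30% | +30 | +9 | 71% |
| 50% | +30 | +15 | 77% |
| 20% | −20 | −4 | 58% |

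The last row is there because more anxious children may be the ones premedicated, and they may report less anxiolysis.

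**Comparison with sampling error.** The 95% half-width of the pooled estimate at 62% is 1.96 × √(0.62 × 0.38 / 1300) = 2.6 points. A shift equals this when s × u = 2.6, for example 0.13 × 20. Smaller combinations stay below it. Larger recruitment narrows the interval but leaves the shift unchanged.

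**Precision if reported by premedication status.** Same formula, 62% in both groups, N = 1300, no allowance for clustering by centre:

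| s | n without | Half-width | n with | Half-width |
|---|---|---|---|---|
| 10% | 1170 | 2.8 | 130 | 8.3 |
| 20% | 1040 | 3.0 | 260 | 5.9 |
| 50% | 650 | 3.7 | 650 | 3.7 |

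These figures are for the first session. Children with a single session complete only the first part of the questionnaire, so last-session intervals will be wider.

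**The case against.** The strongest reply is that the pooled prevalence is what the objective asks for. The study is observational and descriptive, covers hospitals known to differ in practice, has no control group and aims to be representative. Prevalence under routine use is a legitimate target, and labelling anxiolysis an expected effect of EMONO describes the questionnaire list without claiming a cause. This stands, so the pooled figure should not be displaced as the answer to the main objective.

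A second reply is that the SAP, which is not shown, may contain a table by premedication status. It may. However, the article itself says how the main objective is analysed and where premedication enters, and it enters only elsewhere. The point concerns that stated use.

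A third reply is that the safety wording in the Discussion is an expectation with no test or decision rule behind it. That is correct, and it limits the point to interpretation.

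Stronger readings are tempting but not supported:

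- *Sedative effects are being reported as EMONO effects.* The article names no sedative and reports no data on its effect, so a contribution is plausible but not shown.
- *Pooling inflates the prevalences.* If the more anxious children are premedicated, the shift could go the other way.
- *The pilot's 62% is the rate without premedication.* The article does not say so. It serves above only as an illustrative base.
- *Amnesia is among the affected primary effects.* It is a secondary item, assessed at the last session.

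**Conclusion.** The point holds as a limit on interpretation and a cheap improvement. The pooled prevalences are valid for routine use in the participating hospitals. They do not support statements about EMONO given without a sedative, and the Background's own safety statement depends on that distinction.

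The size cannot be computed from the article. The illustrative range of 0.5 to 15 points rests entirely on assumed values of s and u, and the direction is assumed as well. If few children are premedicated or the groups differ little, the shift is smaller than sampling error. Only the breakdown would show which case applies.

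A reader might infer that the main result is wrong or that the children without premedication give a clean causal estimate for EMONO. Neither follows. The objective is descriptive, and premedication is not randomised, so the two groups may differ in baseline anxiety and in centre.

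**What to change.** In Statistical methods (or the SAP):

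1. Keep the pooled prevalence of each effect as the description of routine use.
2. Add, by premedication status at the session concerned, each primary prevalence (felt; felt and pleasant), the prevalence of combined analgesia and anxiolysis, and the secondary last-session prevalence of amnesia. Report the number of children in each group with confidence intervals.
3. Add premedication as a factor in the regression for combined analgesia and anxiolysis, and read its coefficient as an association that may partly reflect centre.
4. Base any statement about EMONO without co-administered sedatives on the group without premedication, and say that the groups are not randomised and may differ in baseline anxiety and centre.

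The cost is some wording and extra columns in the tables. Recruitment, the questionnaire and care are unchanged. Intervals widen slightly without premedication, and more clearly in the premedicated group if it is small (8.3 points at an assumed 10% share).

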## Methods

### Study design

This observational, descriptive, transversal study aims to evaluate the effects sought and felt by children when EMONO is used in paediatric dentistry. Subjects needing dental care under EMONO were recruited by 12 French dental service university hospitals. Thereafter, the data are collected by practitioner observation, direct interview after dental care under EMONO and using the subject’s medical record.

This project received the financial support from the French National Agency for Medicines and Health Products Safety (ANSM) as part of the 2017 ‘national call for tender’ and also received funding from the local Scientific Committee of the Faculty of Dental Surgery in Nantes as part of the 2017 call for tender.

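### The model for children with both analgesia and anxiolysis leaves out pre-inhalation anxiety, although a fall in that score is one of two routes into its outcome

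*Protocol article*

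**What the plan says.** Secondary endpoints (protocol article) builds the outcome from three first-session parameters: "Decreased score on the anxiety scale" from before to after inhalation, anxiolysis among the effects felt, and analgesia among the effects felt. A child is counted when "at least one of the first two parameters and the third parameter are present during the same session of EMONO use". The rule is therefore (score fell OR anxiolysis felt) AND analgesia felt.

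Statistical methods gives the model in one sentence: "A multivariate logistic regression model will be applied to define the associated factors: child/parent socio-demographic characteristics and antecedents". The appetite model in the next paragraph has its own, longer list, which adds the expected effects and how they were perceived. The two lists thus read as choices made for each model.

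Sedative premedication appears elsewhere. Secondary endpoints says that the practices compared between hospitals "will include the use or absence of a sedative premedication and management of the patient in closed or open boxes", and Statistical methods examines their impact on anxiety by Student's tests. It is not a listed factor in the model discussed here.

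**The concern.** A change score depends on where it starts. A child at the lowest anxiety score cannot fall, so that child can enter the outcome only through felt anxiolysis. A child who starts high has two routes, and the score route is easier still because an unusually high reading tends to be followed by a lower one. The outcome therefore depends on the pre-inhalation score by construction, whatever the gas does.

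The score is recorded but does not enter the model. Listed factors that plausibly go with anxiety on arrival, such as age or history, can pick up this dependence. The model exists to say which children obtain both effects. Part of the resulting profile could simply describe children who arrive anxious enough to be able to improve on the scale. Premedication raises a similar confounding question, since the protocol itself treats it as something that may affect anxiety.

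**Working it through.** **The plan's own figures.** None is given for this model. The only computed sample size, 1291 in the Discussion, is for the appetite objective. It reproduces as 1.96² × 0.16 × 0.84 / 0.02² = 1290.7, rounded up, if a half-width of 2 percentage points is inferred (the article does not state one). It has no bearing here. At the pilot's 33% with both effects, 1300 children give 0.33 × 1300 = 429 events, so a few extra terms are affordable.

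**Inputs from the document.** The outcome rule and factor list are as described above. There are 12 centres and a target of 1300 children, taken as 12 × 108 = 1296.

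**Inputs assumed, because the article gives none of them.**
- Share of children at the lowest pre-inhalation score: 5%, 20% or 40%.
- Link between a listed factor and that score: the log-odds of being at the lowest score fall by 0, 0.3 or 0.7 per standard deviation of the factor.
- Probability that the score falls: 0.5 for a child above the lowest score, 0 for a child at it.
- Felt anxiolysis 0.5 and felt analgesia 0.475, independent of each other and of the factor. The factor thus has no effect of its own.

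**Size of the built-in dependence under these inputs.**
- At the lowest score: 0.475 × 0.5 = 0.24.
- Above it: 0.475 × (1 − 0.5 × 0.5) = 0.36.
- Overall, with 20% at the lowest score: 0.2 × 0.2375 + 0.8 × 0.356 = 0.33, matching the pilot's joint prevalence.

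**Simulation.** 400 data sets per scenario, no centre variation, logistic model with the factor alone. Entries are the odds ratio per standard deviation and the rejection rate at 5%.

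| Share at lowest score | No link | Link 0.3 | Link 0.7 |
|---|---|---|---|
| 5% | 1.00, 6.5% | 1.01, 4.5% | 1.02, 7.2% |
| 20% | 1.00, 2.8% | 1.03, 7.0% | 1.06, 16.3% |
| 40% | 1.00, 3.3% | 1.04, 10.0% | 1.09, 30.0% |

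The Monte Carlo standard error of a 5% rate is √(0.05 × 0.95 / 400) = 1.1 points, so rates up to about 7% are hard to tell from nominal.

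When an indicator for being at the lowest score is added, the linked scenarios return to odds ratios of 0.995 to 1.003 and rejection rates of 4.5% to 6.0%.

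**What the simulation leaves out.**
- It models only the floor. Above the lowest score the chance of a fall is constant, so a fall being likelier from a high score is not sized.
- In the other direction, the score route adds 0.475 × 0.5 × 0.5 = 11.9 points above the lowest score. If the pilot percentages were felt effects (the article does not say), only 40 − 33 = 7 points have analgesia without anxiolysis. A fall in half of those children would add 3.5 points, and the bias would be smaller.

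**The case against.** The strongest reply has three parts.

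First, the outcome rule already limits the problem. A child at the lowest score is not excluded, since felt anxiolysis with analgesia suffices. A factor unrelated to anxiety on arrival shows no bias. This stands, and it is why the odds ratios are small.

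Second, the study is descriptive and aims to characterise these children. If anxious arrivals obtain both effects more often, that belongs in the profile. Pre-inhalation anxiety may also lie between age or history and the outcome, so adjusting changes the question from a total to a conditional association. This stands as a reason not to replace the planned model. It does not argue against reporting both models, and it does not separate a real difference in benefit from one that the scale's floor creates.

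Third, a condensed article may leave the final covariates to an analysis plan that is not shown. For this model the article names its factors, and differently from the neighbouring model, so the omission of the score can be read from the text. The same cannot be said of centre. A reader might infer that the standard errors will be too small because no centre term is mentioned for 12 hospitals. The article is silent on centre, and that handling is commonly left to the full plan. The listed factors describe children and parents and vary within hospitals; large variance inflation would arise for a covariate fixed by hospital, and none is listed. Omitting baseline anxiety or premedication is in any case a question of confounding, not of standard errors.

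**Conclusion.** The point holds as a modest weakness of one secondary model. The stated factors omit a collected score on which one route into the outcome depends, so associations with factors tied to anxiety on arrival may be partly built in. Under the assumed inputs the odds ratio for a factor with no effect of its own is about 1.01 to 1.09, with a false-positive rate of about 4.5% to 30%. The upper end needs both a large share of children at the lowest score (40%) and a strong link (0.7). The article gives neither quantity, so the range is illustrative and not a bound.

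A reader might infer that the model's factors will be wrong. The document does not support that: the result runs from no bias to a material false-positive rate, depending on inputs it does not state. A reader might also derive a larger odds ratio from the pilot percentages. That would describe pre-inhalation anxiety itself, not the bias in a listed factor, and it needs the pilot's anxiolysis to have been self-reported, which the Discussion does not say. Nor does the article give the scale's range or name parental anxiety as a factor in this model; it appears under Secondary endpoints for the appetite group.

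**What to change.** In Statistical methods, for the analgesia-plus-anxiolysis model:

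1. Add the pre-inhalation anxiety score and sedative premedication as covariates, and report the model with and without them.
2. Repeat the analysis with the outcome defined as felt anxiolysis plus felt analgesia only.
3. Report the composite's prevalence separately for children at the lowest pre-inhalation score and for those above it.

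The cost is a few extra terms, one sensitivity analysis and one extra table row, all from data already collected. The adjusted coefficients answer a conditional question (which factors matter at a given starting anxiety and premedication status), and the report should say so beside the unadjusted ones.

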EMONO in paediatric dental care is particularly useful in which EMONO can be administered as the first psychoactive substance known for its positive effects (euphoria). Health professionals observe children who take EMONO daily. The main objective of this project is to evaluate the effects sought and felt by children when EMONO is used in paediatric dentistry. The secondary objectives are to (i) evaluate the appreciation of EMONO by a child, (ii) characterize children who experience both analgesia and anxiolysis, (iii) evaluate children’s appetite for EMONO and characterize children with high appetite and (iv) evaluate the impact of various product applications among the French dental service university hospitals on anxiety. The maintenance of the framework for the safe use of this drug, which is placed in dental care as fundamental, and the benefit ratio as very favourable, is essential. Twelve French dental service university hospitals have agreed to set up this study.

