## Discussion

A pilot study was carried out at the Dental Service of Nantes University Hospital, considering most of the parameters that will be used for this national study. It revealed a relatively small number of patients with both anxiolysis and analgesia effects. Sixty-two percent of patients presented an anxiolytic effect, and 40% showed relative analgesia. Both effects were associated in 33% of children. These effects were among the most monitored in patients [43].

Among the 76 patients assessed, 12 attempted to extend the duration of EMONO use (16%), which was considered similar to signalling a higher appetite for the product. After bivariate statistical analysis, none of the variables collected appeared significantly associated with the extension of EMONO use.

Recruiting patients needing EMONO for dental care will not be a challenge for the partners working on the project. The main objective of this project is to evaluate the effects sought and felt by children when EMONO is used in paediatric dentistry. It does not need a precise number of subjects. On the other hand, being able to characterize patients with a higher appetite for EMONO will require 1291 patients from a subject calculation with an alpha risk of 5%. This calculation was made from the results of the pilot study.

The purpose of the study is to evaluate the use of EMONO received only at the hospital. In addition to considering elements of the subject’s medical and family histories, this evaluation includes a semi-structured interview with the subject after its consumption. Given the variability in the study population, the interview will be adapted to the child’s or adolescent’s age, maturity and comprehension skills. The subject’s parent or legal guardian may also be questioned in addition to the subject.

In paediatric dentistry, the use of EMONO in children corresponds in most cases to the first administration of a substance known for its positive effect, euphoria. It seems fundamental to us to evaluate the therapeutic and non-therapeutic effects to better estimate the benefit/risk ratio of the administration. The interest of this evaluation is such that most of the French dental service university hospitals (12/16) responded favourably and wishes to participate in this work. A national study would increase the power and ensure the representativeness of the data collection.

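### Read by the protocol's own definitions, the high-appetite model leaves out euphoria and parental anxiety, and it lists perceptions that exist only for effects felt without saying how they are coded

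*Protocol article*

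**What the plan says.** Four places in the protocol article bear on the model for children with a higher appetite.

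- **Statistical methods.** A multivariate logistic regression is to identify associated factors, listed as "socio-demographic child/parent characteristics, medical history, presence of expected EMONO effects and their perceptions".
- **Primary endpoint.** The effects are questioned in two named groups. The first is "each expected effect of EMONO (waking state preserved, no abolition of judgment, relative analgesia, anxiolysis"; the second is "each adverse event (slight decrease in consciousness, agitation, anxiety, euphoric effect, nausea or vomiting, sensation distortion". Unexpected other effects are also recorded. On perception the section says: "For each effect felt, the patient will be asked about his or her perception of the effect (positive or not".
- **Secondary endpoints.** High appetite means signs that the child tries to prolong contact with EMONO at the first session. Three parameters are to characterize these children: the table of expected effects with their perceptions, the medical history, and the parents' family situation together with their anxiety.
- **Background and Discussion.** The Background says that "EMONO can be administered as the first psychoactive substance known for its positive effects (euphoria". The Discussion says that in most cases EMONO is "the first administration of a substance known for its positive effect, euphoria", and goes on to call for evaluating both therapeutic and non-therapeutic effects.

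**The concern.** The predictor list uses a term that the article has defined. By that definition the effects in the model are the four therapeutic ones, and euphoria falls outside. Children seeking to prolong a drug because it felt euphoric is the obvious link to look for, given how the article motivates the evaluation, yet no stated analysis relates euphoria to appetite. The model could report that no felt effect is associated with appetite without having looked at euphoria.

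Two further problems sit in the same list. Parental anxiety is promised as a characterizing parameter in one section and is absent from the model in another. The list also names presence and perception of each effect side by side, while perception has no value for a child who did not feel the effect. Without a coding rule, software that drops incomplete records would remove those children.

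At stake is the second half of secondary objective (iii), to characterize children with a high appetite. It is also the only aim for which the article states a required number of patients.

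**Working it through.** **1. The plan's own figure.** The Discussion gives 1291 patients at an alpha risk of 5%, based on the pilot, with no power, effect size or precision. Assuming a 95% confidence interval of ±2 percentage points (my assumption) around the pilot's 16%:

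n = 1.96² × 0.16 × 0.84 / 0.02² = 1291.

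With the unrounded 12/76 the result is 1277. The match fits a calculation for estimating a prevalence, but it is not proof: two-group formulas also come close to 1291 when the difference is chosen freely. The article therefore does not show that the number was set with the regression's terms in mind.

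**2. Which effects enter the model.**

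| Item | Group in Primary endpoint | In the Statistical methods list? |
|---|---|---|
| Preserved waking state, retained judgment, analgesia, anxiolysis | Expected | Yes |
| Euphoria | Adverse event | No |
| Decreased consciousness, agitation, anxiety, nausea or vomiting, sensation distortion | Adverse event | No |

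Secondary endpoints also speaks of expected effects only, so the two sections agree with each other. The mismatch is with the rationale in the Background and Discussion.

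**3. Parental factors.** Secondary endpoints names family situation and parental anxiety. Statistical methods names socio-demographic characteristics of child and parent. Family situation can be read into that phrase; parental anxiety is not a socio-demographic characteristic.

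**4. Size of the possible loss through perceptions.** Inputs: recruitment aim 1300 (Study size); from the pilot (Discussion), "Sixty-two percent of patients presented an anxiolytic effect, and 40% showed relative analgesia", both effects in 33%, and high appetite in 12 of 76 (15.8%).

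High-appetite children expected in all: 1300 × 12/76 = 205.

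If perceptions are separate terms and only complete cases are used, the children kept are 1300 × the proportion who felt the effect(s), and the events are that number × 12/76:

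| Perception terms entered | Children kept | Lost | Events kept |
|---|---|---|---|
| Anxiolysis only | 1300 × 0.62 = 806 | 38% | 127 |
| Analgesia only | 1300 × 0.40 = 520 | 60% | 82 |
| Both | 1300 × 0.33 = 429 | 67% | 68 |
| One three-level factor per effect | 1300 | 0% | 205 |

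The pilot gives no prevalence for the other two expected effects. Assuming 50% to 100% for each, independent of the rest, all four perceptions would keep 1300 × 0.33 × 0.5 × 0.5 = 107 up to 429 children, with 17 to 68 events.

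Among the children kept with both perceptions, the presence of both effects is constant. The association of presence with appetite could then not be estimated at all.

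**The case against.** The strongest reply has four parts.

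- **The coding is not fixed.** The article prescribes neither separate perception terms nor complete-case analysis, and an analysis plan that is not shown may settle both. The descriptive analysis already reports the proportion who felt an effect and found it pleasant, a combined measure that can be defined for every child. This stands. A reader might infer from the table above that most children will be lost, but the documents do not support that.
- **Euphoria is not ignored.** Its prevalence and pleasantness are reported under the main objective, and no passage states a hypothesis that euphoria drives attempts to prolong EMONO. This also stands. A reader might conclude that the study cannot address its central dependence question. That goes too far: the main objective is descriptive, appetite is a secondary objective, and the gap concerns one regression.
- **The term may be meant loosely.** Because the Primary endpoint section sets the listed items against unexpected other effects, expected could mean everything on the list. This is possible, but the same section applies the word to the four therapeutic effects and gives the adverse events their own label. At best the term is ambiguous, and the wording still needs correcting.
- **Parental anxiety is a small mismatch.** It is already a declared parameter and will at least be described. This is fair as to size. The two sections still disagree about what characterizes these children.

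The general reply that predictors belong in the analysis plan does not dispose of the point. The article has already chosen them, and a plan faithful to it would inherit the exclusion. Adding euphoria after the data are seen would be post hoc.

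**Conclusion.** The point holds for the predictor list. Read by the article's own definitions, the high-appetite model contains neither euphoria nor parental anxiety. The first omission sits badly with the stated rationale; the second contradicts the Secondary endpoints section.

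The perception problem is a conditional risk. In the unfavourable case, with separate terms for analgesia and anxiolysis on complete cases, at most 429 of 1300 children and about 68 of 205 events remain; with three-level coding nothing is lost. These figures assume that the full 1300 are recruited and that the single-centre pilot rates hold nationally. The event counts further assume that appetite is unrelated to the effects felt.

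The main descriptive results, data collection and sample size are not affected.

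**What to change.** In Secondary endpoints and Statistical methods, use one identical predictor list for the high-appetite model:

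- socio-demographic characteristics of child and parent, and medical history;
- family situation and parental anxiety, both named;
- the four expected effects and the euphoric effect, all named;
- the other listed adverse effects as far as the number of events allows.

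Code each effect as one factor with three levels: not felt / felt, not pleasant / felt, pleasant. State this in place of separate presence and perception variables.

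**Cost.** No new data are needed. A three-level factor uses 2 parameters, so the four expected effects take 8, the same as separate presence and perception terms. Euphoria adds 2. The other five adverse effects would add 10, giving 20 parameters for the effects alone, or 205 / 20 ≈ 10 expected events per parameter before any other predictor. That is why euphoria should be named first and the remaining adverse effects made conditional on the events available, with a rule set in advance for merging sparse levels.
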